### Study aim

In the present project, the *In*hibition *Tra*ining (INTRA) study, 246 recently abstinent patients with AUD attending an inpatient treatment program will be randomly assigned to one of two alcohol-specific inhibition training groups (each with a different Go/NoGo ratio) or to a control group. Our aim is to examine whether variations of inhibition training have a positive effect on drinking behavior, implicit attitudes, and neurophysiological reactivity to alcohol-related stimuli. Thus, a subgroup of patients will additionally undergo EEG recording before and after the intervention so that neurophysiological effects of the training can be assessed and related to clinical outcomes. In addition, 50 healthy controls (with EEG measurement of 20) will be assessed once to compare patients’ pre-training data. Since training effects rely on learning processes, the influence of endogenous cortisol level (a consolidation enhancer, which peaks in the morning and decreases in the course of the day [44]) on training outcome will be investigated by varying the time of day in which the training is performed. All patients’ inhibition and implicit associations towards alcohol will be measured immediately before and after the training. We will also measure the training’s effects on proximal outcome variables (e.g., implicit associations, inhibitory control, abstinence-related self-efficacy, craving) post training, and distal outcome variables (e.g., percentage of days abstinent – PDA; heavy-drinking days – HDD; and time to first drink – TFD) at 3-, 6- and 12-month follow-ups.

For the first time, this trial will investigate the therapeutic potential of an alcohol-specific inhibition training as a therapeutic supplement in a sample with patients suffering from severe AUD. In doing so, the impact on training efficacy of time of training and Go/NoGo ratio will additionally be investigated and the underlying neurophysiological mechanisms of the training elucidated. Moreover, potential AUD-related psychological constructs will be explored. The project thus aims to contribute to the improvement of the evidence-based treatment of AUD.

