### Research questions

Based on prior research, the following five research questions are examined:Does the alcohol-specific inhibition training (Alc-IT, compared to the control intervention) reduce PDA and HDD and/or extend the time to first drink (TFD) at 3-months’ follow-up (primary outcomes)?What is the effect of the Alc-IT on behavioral experimental parameters?Does Alc-IT decrease positive implicit associations compared to the control training?Does Alc-IT enhance response inhibition compared to the control training?Are the neurophysiological correlates of alcohol-specific inhibition and implicit associations towards alcohol changed by Alc-IT?Does endogenous cortisol moderate the effect of the Alc-IT?In addition, explorative questions investigate whether the effects of the training on outcomes are mediated by AUD-related psychological constructs, such as alcohol-related self-efficacy, craving or motivation

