#### Training (intervention)

During weeks 4 and 5 of the treatment, all patients will undergo six short training sessions according to their allocated training version (Alc-IT (75/25), Alc-IT (50/50) or control group, either in the morning or afternoon). All training sessions will be distributed over 2 weeks, performed in a group setting, and monitored by a member of the study team. At the beginning of the first session, participants undergo a short practice version to confirm that they understood the task. Before and after each training session, stress and craving will be assessed (see also T2). At the end of each training session, the study member will take note of the participants’ reaction time and error rate, with the aim to maintain motivation. In order to assess saliva cortisol concentration for the cortisol substudy, saliva samples of 80 patients of the Suedhang Hospital will be collected before and after the first training.

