### Procedure for substudies

#### Cortisol substudy

Inclusion and exclusion criteria for the substudy match those of the main study. The first 80 patients who are recruited in the Suedhang Hospital will be additionally asked to participate in the cortisol substudy, which involves collecting a salvia-cortisol sample before and after the first training session.

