#### Main study

Training effects on our primary outcome measures (PDA and HDD at 3-month follow-up) will be assessed with a 2 × 3 analysis of variance (ANOVA) with the factors time point (T1, T5) and training group (Alc-IT (50/50), Alc-IT (75/25) or control). Further, a Cox regression will be computed to predict the effect of the intervention on TFD (at 3-month follow-up).

Training effects on experimental test parameters will be assessed with a 2 × 2 × 3 repeated measures ANOVA with the factors measurement point (T2, T3), time of day (morning, afternoon) and training group (Alc-IT (50/50), Alc-IT (75/25) or control). Where Mauchly’s test of sphericity indicates heterogeneity of covariance, we will verify repeated measures results with Greenhouse-Geisser corrections.

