#### Cortisol substudy

Salivary cortisol concentrations are determined by a commercially available chemiluminescence immunoassay (CLIA; IBL, Hamburg, Germany). Inter- and intra-assay coefficients of variation are both below 8%. For biochemical analyses of free cortisol concentration, saliva samples will be thawed and spun at 3000 rpm for 10 min to obtain 0.5–1.0 ml of clear saliva with low viscosity.

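### The cortisol question is tested through a morning/afternoon factor, which can support conclusions about time of day but not about cortisol level

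*Protocol article*

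**What the plan says.** Protocol article, Research questions, lists among its questions: "Does endogenous cortisol moderate the effect of the Alc-IT". Study aim gives the method: the influence of cortisol level "on training outcome will be investigated by varying the time of day in which the training is performed", on the ground that cortisol peaks in the morning.

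Under Statistics, Main study, the task outcomes are analysed with a "2 × 2 × 3 repeated measures ANOVA with the factors measurement point (T2, T3), time of day (morning, afternoon) and training group". The drinking outcomes PDA and HDD are analysed with a "2 × 3 analysis of variance (ANOVA) with the factors time point (T1, T5) and training group", which has no time-of-day factor, and none is named for the Cox regression of time to first drink.

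Cortisol itself is measured in a substudy. Training (intervention) states that "saliva samples of 80 patients of the Suedhang Hospital will be collected before and after the first training", that is, at the first of six sessions. The Cortisol substudy paragraph under Statistics covers the assay and sample preparation ("Salivary cortisol concentrations are determined by a commercially available chemiluminescence immunoassay").

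The Discussion closes by presenting the trial as one that examines whether endogenous cortisol might strengthen the training effect.

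**The concern.** The question and the intended conclusion are about a hormone level. The stated test is about a time slot. Even if slot is randomly assigned, the comparison identifies the effect of the whole slot. Reading it as cortisol also requires that nothing else relevant to training differs between morning and afternoon. Alertness, fatigue and the ward programme are obvious candidates.

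Two wrong conclusions are possible. A slot-by-version effect could be taken as evidence that cortisol enhances the training. A null slot effect could be taken as evidence that cortisol does not matter, although patients within the same slot may differ in cortisol and benefit accordingly.

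**Working it through.** **1. The plan's own figure.** The only stated analysis with time of day is the repeated-measures ANOVA, for which Power calculation gives n = 180. Inputs from that section: f = 0.15, correlation 0.4 among repeated measures, α = 0.05, power 0.80. The design gives m = 2 measurements and 3 × 2 = 6 groups. For the within-between interaction:

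- λ = f² · N · m / (1 − ρ), with df1 = 5 and df2 = N − 6.
- The first N with power of at least 0.80 is 177, or 180 when rounded up to a multiple of 6.
- At N = 180: λ = 0.0225 × 180 × 2 / 0.6 = 13.5, df2 = 174, power 0.809.

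So 180 is reproduced. It is built on slot as a design factor and contains no cortisol term. The issue is what the test identifies, not its arithmetic.

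**2. What the slot contrast identifies.** Let γ be the change in training effect per unit of log cortisol, d the mean morning–afternoon difference in log cortisol, and κ the change in training effect from everything else that differs between slots. Assuming a linear relation, the slot-by-version contrast is

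Δ = γ · d + κ.

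The ANOVA estimates Δ only. Δ ≠ 0 is compatible with γ = 0 (all of it κ). Δ = 0 is compatible with γ ≠ 0 (small d, or κ offsetting γ · d). The stated rationale, a morning peak, supports d ≠ 0 but says nothing about κ. The documents do not say how closely slot tracks cortisol in these patients, so no figure can be put on the share that slot captures.

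**3. What the measured cortisol could support.** It is available in 80 of 246 patients (80/246 = 33%), from one hospital, at 1 of 6 sessions. That is 80/3 ≈ 27 per training version and 80/6 ≈ 13 per version and slot.

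Assumed model: intercept, cortisol, two version terms and two cortisol × version terms, so df1 = 2, df2 = 80 − 6 = 74 and λ = f² · 80.

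| f | λ | Power at n = 80 | N for 80% power |
|---|---|---|---|
| 0.15 | 1.8 | 0.20 | 432 |
| 0.20 | 3.2 | 0.33 | 244 |
| 0.25 | 5.0 | 0.49 | 158 |

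The smallest f with 80% power at n = 80 is about 0.355. These figures leave out slot and slot × version. Adding those terms leaves only within-slot variation in cortisol to inform the interaction, so they should be read as approximate and probably favourable.

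**The case against.** The strongest defence is that this is a recognised design: shift an endogenous hormone by scheduling, and measure it in a subsample to support the interpretation. The abstract says that time of training is randomly assigned. The dedicated sampling, storage and assay suggest that the values are meant to be used, and a journal article commonly leaves a substudy model to the full protocol or analysis plan.

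Much of this stands, and it rules out three stronger readings.

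- A reader might infer that the measured cortisol will never be analysed. The documents do not support that. The Statistics paragraph on cortisol names no model, but one may exist in a document not shown.
- A reader might infer that a time-of-day result will be reported as a cortisol effect. That is a risk, not a stated intention. The abstract, the second paragraph of Study aim, Main study and Power calculation all speak of training time or time of day.
- A reader might infer that the post-session sample will serve as the moderator, although it follows exposure to the training. The plan says only that it is collected.

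The defence does not answer the explicit method in Study aim combined with the cortisol wording in Research questions and the Discussion. An unseen model would not correct that wording. The design argument also depends on slot being randomised. Randomization and blinding describes assignment to three arms and does not name time of day, whereas the abstract describes six arms. Those sections need reconciling; if slot is not randomised, the proxy is weaker still.

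**Conclusion.** The point holds as a mismatch between question and stated test. The morning/afternoon comparison in the task outcomes identifies a time-of-day effect. It neither establishes nor excludes moderation by cortisol level. This follows from the design and does not depend on any assumed correlation between slot and cortisol.

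Severity is minor. The cortisol question is one of the named research questions, but the analyses of PDA, HDD and time to first drink and the three sample-size calculations are unaffected. The power range of about 0.20 to 0.49 rests on the assumed model above and on effect sizes of f = 0.15 to 0.25. It means that the cortisol result should be read as an estimate, not a confirmatory test.

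**What to change.** 1. Reword Study aim and the closing part of the Discussion so that the 246-patient morning/afternoon comparison supports conclusions about time of day only.

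2. For the cortisol question, in the 80 substudy patients, model the T3 task outcome adjusted for T2, with training version, log pre-session cortisol, cortisol × version, slot and slot × version. Report the cortisol × version estimate with its confidence interval. The slot × version term is needed: with slot only as a main effect, any slot-related difference in training benefit would load onto cortisol × version, because slot and cortisol are related.

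3. Report the morning/afternoon difference in pre-session cortisol as a manipulation check.

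4. Label the cortisol result exploratory. Within slot it is observational, it comes from one hospital and the first session only, and power is low.

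If a cortisol model already exists in the full protocol or analysis plan, check it against these terms.

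The cost is one regression and one descriptive comparison on samples already planned, plus wording. The article places the main analyses after data collection and reports collection as still under way, so the model could be fixed before results are seen. The downside is a more modest cortisol claim.

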### Research questions

Based on prior research, the following five research questions are examined:Does the alcohol-specific inhibition training (Alc-IT, compared to the control intervention) reduce PDA and HDD and/or extend the time to first drink (TFD) at 3-months’ follow-up (primary outcomes)?What is the effect of the Alc-IT on behavioral experimental parameters?Does Alc-IT decrease positive implicit associations compared to the control training?Does Alc-IT enhance response inhibition compared to the control training?Are the neurophysiological correlates of alcohol-specific inhibition and implicit associations towards alcohol changed by Alc-IT?Does endogenous cortisol moderate the effect of the Alc-IT?In addition, explorative questions investigate whether the effects of the training on outcomes are mediated by AUD-related psychological constructs, such as alcohol-related self-efficacy, craving or motivation

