### Power calculation

The intended sample size was calculated with G*Power (Version 3.1.5, Heinrich-Heine-University Duesseldorf, Dusseldorf, Germany). In a-priori analyses (1−β = 0.8, α = 0.05), slightly reduced expected effect sizes were entered compared to earlier studies because of the additional manipulations concerning different training versions and time of training. For the 2 × 3 ANOVA to examine the training effects on the primary outcome measures PDA and HDD (with an expected effect size of f = 0.2 based on earlier studies [32]), a total sample size of *n* = 244 is needed. For the analyses of the training’s effect on TFD (the third primary outcome, estimating a small to medium effect size of w = 0.25 based on earlier studies [37], and df = 3), G*Power indicated a total sample size of *n* = 174 for the Cox regression. For the 2 × 2 × 3 repeated measures ANOVA examining training effects on experimental parameters and also taking into account the effects of time of day of the training (expecting small to medium effects of f = 0.15 and correlations of 0.4 among repeated measures based on earlier studies [107]), the necessary sample size was *n* = 180. Considering the necessary power for all analyses and similar sample sizes in all study arms (82 per intervention group), a total of 246 patients will be recruited.

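### The primary question states the wrong direction for PDA and joins three primary outcomes by and/or, each sized at the full 5%, with no rule for combining them

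*Protocol article*

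**What the plan says.** Under Research questions, the first question asks whether alcohol-specific training, compared with control, will "reduce PDA and HDD and/or extend the time to first drink (TFD") at the 3-month follow-up, and labels these the primary outcomes. Study aim expands the abbreviation as "percentage of days abstinent – PDA" and gives the general aim as a favourable effect on drinking behaviour.

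The Main study part of the Statistics section says "Training effects on our primary outcome measures (PDA and HDD at 3-month follow-up) will be assessed" with a 2 × 3 ANOVA. Its next sentence adds a separate Cox regression for TFD.

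The Power calculation gives one setting for all sizings: "In a-priori analyses (1−β = 0.8, α = 0.05"). For PDA and HDD it works "with an expected effect size of f = 0.2 based on earlier studies [32"] and concludes that "a total sample size of *n* = 244 is needed". TFD is "the third primary outcome, estimating a small to medium effect size of w = 0.25" with df = 3, which gives 174. Recruitment is 246, or 82 per intervention group.

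The article states no lead outcome, testing order, joint-success rule or division of alpha for the three primaries. The only multiplicity control it mentions is for the EEG randomization tests.

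**The concern.** There are two faults in one sentence.

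**Direction.** Fewer heavy-drinking days is a benefit; fewer abstinent days is a harm. One verb covers both, so the question taken at its word counts a loss of abstinence as the hoped-for result. The planned ANOVA is an omnibus test with no direction of its own, so the direction has to come from the stated hypothesis.

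**Combination.** Three outcomes are primary, they are tested in separate analyses, and the connective leaves open which pattern of results would answer the question with yes. If a single significant outcome is enough and each is tested at 5%, the chance of a false primary claim exceeds 5%. If the choice is left until the results are known, the emphasis can follow whichever outcome did best.

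**Working it through.** **Inputs.** From the Power calculation: alpha 0.05, power 0.80, f = 0.2, N = 244 (PDA and HDD); w = 0.25, df = 3, N = 174 (TFD); 246 recruited. From Research questions: three primary outcomes. The documents give no correlation between them, so it is varied below as an assumption.

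**1. Do the stated sample sizes use the full 0.05?**

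- PDA/HDD: noncentral F, numerator df 2, λ = N·f². At N = 244, λ = 244 × 0.04 = 9.76 and power is 0.800. N = 244 is the smallest that reaches 0.80, whether the denominator df assume 3 or 6 cells. At 246, power is 0.804.
- TFD: noncentral chi-square, df 3, λ = N·w². At N = 174, λ = 174 × 0.0625 = 10.875 and power is 0.799. The smallest N reaching 0.80 is 175, so 174 is reproduced within rounding.
- With alpha 0.05/3 = 0.0167 instead, power at these same Ns is about 0.66 for each.

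The stated Ns therefore fit unadjusted 5% tests and not an equal split.

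**2. Family-wise error if any one significant outcome counts**

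- Independent: 1 − 0.95³ = 0.143. Ceiling under any dependence: 3 × 0.05 = 0.15.
- Common positive correlation r, by simulation of three correlated 2-df chi-square statistics (three groups), each tested at 5%:

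| r | Any of three |
|---|---|
| 0.3 | 0.137 |
| 0.5 | 0.127 |
| 0.7 | 0.111 |
| 0.8 | 0.101 |
| 0.9 | 0.085 |

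**3. Family-wise error if the sentence is read literally as (PDA and HDD) or TFD**

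- All independent: 0.05 + 0.05² − 0.05³ = 0.052.
- Common correlation of 0.3 to 0.9, same simulation: 0.054 to 0.058.
- PDA and HDD always agreeing, TFD independent: 1 − 0.95² = 0.0975.
- Ceiling: 0.05 + 0.05 = 0.10.

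**4. What a correction costs at 246**

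- At alpha 0.0167, with λ = 246 × 0.04 = 9.84 and df 2, 243, PDA/HDD power is 0.663; 319 patients would restore 0.80.
- For TFD at the same alpha, power at 246 is 0.843; 225 patients would suffice for 0.80.
- In a fixed order with each test at 0.05, the first outcome keeps its full power at 246: 0.804 if it is PDA or HDD.

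**5. Direction.** This needs no arithmetic. Study aim defines PDA as a percentage of abstinent days and wants drinking behaviour to improve; Research questions asks whether PDA is reduced. The two cannot both stand.

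**The case against.** The strongest reply is that no success rule is written down. A research question is not a decision rule, and the only alpha appears in the sample-size section, so testing each outcome at 5% is an inference from the sizing. A statistical analysis plan that is not shown may settle multiplicity. Sizing each outcome at 0.05 is also compatible with a fixed testing order. All of this stands, and it is why the error rate is given as a range tied to how the sentence is read. It does not remove the point: the article itself fixes three primaries, an ambiguous connective and sample sizes that leave no room for an equal split at 80% power for PDA/HDD.

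Three stronger readings are tempting and are not supported:

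- **That the error rate simply is 14%, or two to three times nominal.** That needs both the any-of-three reading and independence. All three outcomes come from the same Timeline Follow-back interview, and a patient abstinent throughout has PDA of 100%, no heavy-drinking days and no first drink. At r = 0.9 the rate is 0.085, or 1.7 times nominal. The literal reading never exceeds 10%.
- **That the Statistics section drops TFD as a primary outcome.** Its parenthesis names the outcomes analysed by ANOVA, the next sentence analyses TFD, and the Power calculation calls TFD the third primary. This is loose phrasing.
- **That the reversed direction would change the analysis.** The omnibus ANOVA and the sample size are the same either way, and the intent can be read from Study aim. The wording is still wrong in the sentence that poses the primary question.

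**Conclusion.** The concern holds in this form. The direction error for PDA is certain from the text. The missing combination rule is a real weakness whose size depends on the reading: about 8 to 14% family-wise error if any one of three outcomes suffices, and about 5 to 6% under common correlation, at most 10%, if PDA and HDD must both succeed or TFD alone does. These figures assume that each test is run at 5%, as the sizing implies, and that the correlations lie between 0 and 0.9; the documents give none. Nothing in the article establishes which reading is meant, and that ambiguity needs to be closed. A reader might infer that the trial has no multiplicity control at all; the documents at hand show only that the article states none for the primary outcomes.

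**What to change.** - Reword the first research question so that the training is asked to increase PDA, reduce HDD and extend TFD.
- Name the same three outcomes as primary in the Main study part of the Statistics section.
- Before unblinding, replace the and/or by one rule that holds the overall error at 5%: either Holm across the three omnibus tests, or a fixed testing order with each test at 0.05, stopping at the first non-significant result. The documents give no basis for a particular order, so the sponsor should choose and justify it.

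The cost is wording only. The article reports data collection as still under way and places the main analyses after its completion. Each rule has a price. Under a fixed order, later outcomes cannot be claimed once an earlier one fails. Under Holm, power at 246 can fall at the first step to about 66% for PDA/HDD (f = 0.2) and about 84% for TFD (w = 0.25, df = 3), and the stated 80% would have to be restated.
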